## Abstract

**Objective::**

Research studies have examined saffron's effects on inflammation, infection, and oxidative stress. Nevertheless, the effects of saffron on sepsis patients in the intensive care units (ICUs) have not yet been studied. Hence, this study will examine the effects of saffron supplementation on oxidative stress biomarkers, inflammation factors, and clinical outcomes in critically ill septic patients.

**Materials and Methods::**

Ninety patients with sepsis will participate in this parallel double-blind, randomized clinical controlled trial. In addition to usual care, the intervention group (n=45) will receive a daily tablet containing 100 mg/day saffron for 7 days, and the control group (n=45) will receive a placebo tablet containing 100 mg/day corn starch for the same duration. Acute Physiology and Chronic Health Evaluation II (APACHE II), the Sequential Organ Failure Assessment (SOFA), and the NUTRIC Score will be used to assess the patients' clinical and nutritional status at the beginning and end of the study. Inflammatory markers including erythrocyte sedimentation rate (ESR), C-reactive protein (CRP), interleukin (IL)-6, tumor necrosis factor-alpha (TNF-α), and IL-18, indicators of oxidative stress including malondialdehyde (MDA), glutathione peroxidase (GPx), catalase, superoxide dismutases (SODs), and total antioxidant capacity (TAC), level of Glasgow Coma Scale (GCS), complete blood count (CBC), and lactate dehydrogenase (LDH) will be evaluated at beginning and end of the study. Twenty-eight days after the start of the intervention mortality rates will be assessed.

**Discussion::**

Due to the anti-inflammatory, antioxidant, and antimicrobial effects, saffron might have beneficial effects in critically ill patients with sepsis.

## Introduction

Sepsis is among the most frequent reasons for admission to intensive care units (ICUs) (Genga and Russell 2017). Furthermore, it is one of the leading causes of morbidity and mortality among ICU patients (Sakr et al. 2018). According to recent research, sepsis is a final common cause of infection-related death (Schlapbach et al. 2020). Globally, the incidence of sepsis has been on the rise (Navaneelan et al. 2016). Around 30 million people worldwide suffer from sepsis each year, and more than 6 million people die from it (Organization 2018). In 2011, the United States spent more than $20 million treating septic shock and severe sepsis (Lagu et al. 2012).

 Sepsis is characterized by an uncontrolled and severe immune response to pathogens (bacteria, fungi, parasites, and viruses) (Nedeva 2021). The severity of immune dysfunction and hemostasis problems (coagulation factors and platelets) can lead to cellular and tissue damage, multi-organ failure, and eventually death (Levi and van der Poll 2017). Inflammatory biomarkers and pro-inflammatory cytokines such as interleukin (IL)-6, C-reactive protein (CRP), IL-1, IL-18, and tumor necrosis factor alpha (TNF-α), increase after the development of sepsis (Beltrán-García et al. 2022; Grondman et al. 2020; Mierzchala-Pasierb et al. 2019). Therefore, it is necessary to control inflammation and prevent sudden exacerbation of inflammation and oxidative stress among patients hospitalized in the ICU. 

Despite the availability of antibiotics and fluid resuscitation therapies as effective treatments for sepsis (Brown and Semler 2019), sepsis and its associated complications remain a significant problem in the ICU. Previously, antibiotics have been demonstrated to be insufficient to control the complex mechanism of sepsis (Usmani et al. 2021). In addition, the overuse of antibiotics may result in the emergence of antibiotic-resistant pathogens (Rhee et al. 2020). Based on previous studies, various medicinal plants have the potential to suppress pro-inflammatory and anti-inflammatory cytokines, and the secondary effects of these compounds are minimal or nonexistent (Garnier and Shahidi 2021). Hence, due to the less/no side effects and ease of preparation of medicinal plants, natural compounds have attracted significant interest as an adjunctive therapy to combat the symptoms of sepsis. One of these medicinal plants is saffron (Cardone et al. 2020).

Saffron (Crocus sativus L), a member of the Iridaceae family, is commonly used in food as a flavoring (Khorasanchi et al. 2018). In saffron, more than 150 volatile compounds are present, including carotenoid pigments (crocin, carotene, zeaxan-thin, crocetin, and lycopene), as well as monoterpene aldehydes (safranal and picrocrocin) and monoterpenoids (crocusatines), isophorones, and flavonoids that may contribute to its wide range of biological effects (Asbaghi et al. 2021; Melnyk et al. 2010). Among its active components, particularly crocetin and crocin, are powerful antioxidants and radical scavengers (Puglia et al. 2019). Several studies have revealed the antioxidant, anti-inflammatory, anti-thrombotic, anti-apoptotic, immune system modulatory, and antimicrobial properties of saffron (Asbaghi et al. 2021). Saffron was found to improve erythrocyte sedimentation rate (ESR), CRP, TNF-alpha, malondialdehyde (MDA), and total antioxidant capacity (TAC) levels in rheumatoid arthritis (RA) patients when administered 100 mg daily (Hamidi et al. 2020). The results of a meta-analysis indicated that supplementing with saffron is more beneficial to people with high levels of CRP (Asbaghi et al. 2021).

To our knowledge, no clinical trials have examined saffron's effect on patients with sepsis. This study aims to determine whether saffron supplementation affects inflammatory factors, oxidative stress, and clinical outcomes in patients with sepsis in the ICU. It is hoped that the results of this research can reduce some of the major problems of sepsis patients in the ICU.

## Materials and Methods

This study protocol was developed following the Standard Protocol Items: 

Recommendations for Interventional Trials (SPIRIT) 2013 checklist (Chan et al. 2013). It is a randomized, parallel, two-arm, double-blinded, and placebo-controlled clinical trial that will include 90 critically ill patients with sepsis. Figure 1 illustrates the trial design. From May 2024, patients will be selected from the ICU of Al-Zahra Hospital, an academic hospital affiliated with Isfahan University of Medical Sciences, Isfahan, Iran. We will screen subjects according to our inclusion and exclusion criteria before including them in the study. 

### Eligibility criteria

The following criteria will be used to select participants:

### Inclusion criteria

Patients with sepsis who are admitted to the ICU. A diagnosis of sepsis and septic shock will be made using Sepsis-3 definitions by Surviving Sepsis Campaign International Guidelines for Management of Sepsis and Septic Shock (Rhodes et al. 2017) and a confirmation specialist in anesthesiology or infectious diseases. Within 24 hours of diagnosis, septic patients will be recruited. Aged 18 to 80 years old. A legal guardian must write informed consent. Being able to tolerate enteral nutrition and having a normal digestive function. 

### Exclusion criteria

Dissatisfaction of the patient or his legal guardian. Patients who stay in the ICU for <48hr. Patients receiving parenteral nutrition. Patients receiving enteral or oral nutrition initially but transferring to parenteral nutrition due to contraindications. Patients who are incapable of receiving enteral nutrition or who may not be able to receive enteral nutrition in the future as a result of incomplete resuscitation and hemodynamic instability or gastrointestinal disorders such as nausea, persistent vomiting, ileus, obstruction of the intestinal tract, diarrhea that exceeds 500 ml per day, and high-output fistulas. Cancer patients undergoing chemotherapy. Patients suffering from pancreatitis, kidney failure, or congenital or immune disorders. Patients taking phenobarbital, levetiracetam, or phenytoin. Dialysis patients, patients with severe septic shock or sepsis, or DIC (diffuse intravascular coagulation). Pregnancy and breastfeeding. Patients with BMI < 18.5 kg/m^2^. Patients who need blood transfusions frequently. Unwanted side effects associated with taking supplements or placebos. ICU patients who are expected to die within 2 days of admission. Patients who take other herbal supplements. Patients with a spice or herbal supplement allergy. Patients with GCS levels less than 3 or greater than 13. Patients who passed away during the trial

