### Outcome assessment

Our primary outcomes will be serum levels of CRP, TNF-α, IL-6, IL-18, and ESR as a marker of inflammation, serum LDH as an indicator of cell damage, TAC, SOD, GPx, MDA and catalase as an indicator of oxidative stress that will be measured at the beginning and end of the study. In addition, the 28-day mortality rate, GCS, CBC, APACHE II Score, SOFA score, and NUTRIC score are secondary outcomes. Anthropometric variables including weight, height, body mass index (BMI), and calf circumference will be assessed at baseline of the study (Table 1). Mid arm circumference (MAC) will be assessed at baseline and end of the study. 

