### Statistical methods

SPSS version 22 (SPSS Inc., Chicago, IL, USA) will be used to perform the analysis. For quantitative data, mean and standard deviation (SD) will be reported, and for qualitative data, frequency and percent will be reported. Kolmogorov-Smirnov test will be used to determine whether variables had a normal distribution (Ahad et al. 2011). Paired t-test will be applied to evaluate the differences in each group before and after the intervention. Independent t-test will be used to show the baseline and endpoint differences between the two groups. The Kruskal Wallis test will be used for the between-groups comparison, and the Wilcoxon Ranked Sum test for the inter-group comparisons, if the distribution of data is not normal. We will apply analysis of covariance (ANCOVA) to show differences between two treatment groups after adjusting for confounding variables. For missing data, an intention-to-treat analysis will be performed (Herman et al. 2009). Statistical significance is defined as a p-value less than 0.05.

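### Death during the trial and side effects of the tablets are listed as exclusion criteria, which contradicts the intention-to-treat analysis and removes deaths from the 28-day mortality outcome

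*Protocol article*

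**What the plan says.** Under Eligibility criteria, the protocol introduces its lists as the means of selecting participants. The Exclusion criteria then include four lines that matter here:

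- "Patients who passed away during the trial"
- "Unwanted side effects associated with taking supplements or placebos"
- "Patients who stay in the ICU for <48hr"
- "Patients receiving enteral or oral nutrition initially but transferring to parenteral nutrition due to contraindications"

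On timing, the Inclusion criteria state: "Within 24 hours of diagnosis, septic patients will be recruited". The Intervention section calls the seven days of dosing the trial.

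On outcomes, Outcome assessment states that "the 28-day mortality rate, GCS, CBC, APACHE II Score, SOFA score, and NUTRIC score are secondary outcomes". The Abstract adds: "Twenty-eight days after the start of the intervention mortality rates will be assessed". A separate section says that this follow-up is done by phone.

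On the analysis, Statistical methods says: "For missing data, an intention-to-treat analysis will be performed". Nothing in the protocol says that an excluded patient stays in any analysis, or that the death line applies only to the laboratory markers.

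**The concern.** An exclusion criterion applied after randomisation changes who is compared. Death is also an outcome of this trial, and side effects arise from the tablets themselves, so both may depend on the assigned arm. If such patients are taken out, the groups compared are no longer those that randomisation formed, and the intention-to-treat label does not describe the analysis.

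The mortality outcome is hit most directly, because a patient removed for dying leaves both the numerator and the denominator. There is also a practical risk: patients treated as excluded may not be followed, so a later reanalysis might not recover them.

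The sentence on missing data adds a second problem. Intention-to-treat defines which patients are analysed and in which arm. It supplies no value for a patient without a day-7 measurement, so it cannot serve as the method for missing data.

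**Working it through.** **Step 1: when can each exclusion be known?**

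| Exclusion line | Knowable before randomisation? |
|---|---|
| Death during the trial | No |
| Side effects of supplement or placebo | No; they need at least one dose |
| ICU stay under 48 h | Not timed; sometimes |
| Transfer to parenteral nutrition | Not timed; sometimes |

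The recruitment window runs from diagnosis, not from ICU admission. A patient may therefore already have spent 48 hours in the ICU when recruited, or may have changed feeding route before screening. As written, both lines also apply to a patient who leaves the ICU early or changes route after randomisation.

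**Step 2: which deaths are lost?** If the trial means the seven treatment days, deaths in days 1 to 7 are lost. If it includes follow-up, all deaths are lost and 28-day mortality is 0% in both arms by construction. Under either reading, the exclusion conflicts with the planned mortality outcome.

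**Step 3: illustration for mortality.** The protocol gives no death rate and no timing of deaths, so the inputs here are assumptions. Let p be the true 28-day mortality in an arm and f the share of its deaths that fall in the excluded period. The observed rate is

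p_obs = p(1 − f) / (1 − pf).

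Assume p = 30% in the control arm and 20% in the saffron arm, with the same f in both. For f = 0.5:

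- Control: 0.30 × 0.5 / (1 − 0.15) = 0.15 / 0.85 = 17.6%
- Saffron: 0.20 × 0.5 / (1 − 0.10) = 0.10 / 0.90 = 11.1%

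| f | Control | Saffron | Observed difference (true: −10 points) |
|---|---|---|---|
| 0.25 | 24.3% | 15.8% | −8.5 points |
| 0.50 | 17.6% | 11.1% | −6.5 points |
| 0.75 | 9.7% | 5.9% | −3.8 points |
| 1.00 | 0% | 0% | 0 |

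The error need not be a dilution. Assume equal true mortality of 30%, with 40% of control deaths and 70% of saffron deaths in the excluded period:

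- Control: 0.30 × 0.6 / (1 − 0.12) = 0.18 / 0.88 = 20.5%
- Saffron: 0.30 × 0.3 / (1 − 0.21) = 0.09 / 0.79 = 11.4%

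A false benefit of about 9 points appears. It reverses if the timing is swapped between the arms.

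**Step 4: the attrition allowance.** The protocol plans 35 per group and enrols 45, without stating a rate. That is 1 − 35/45 = 22.2% if the number was divided by (1 − rate), or 45/35 − 1 = 28.6% if it was multiplied by (1 + rate). Either way, 10 patients per arm can be lost before the planned 35 is reached. The figure of 35 cannot be reproduced, because a difference of 3 in CRP is given without an SD.

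**The case against.** The strongest reply is that the list mixes eligibility with rules for stopping tablets, and that the authors will still count deaths. They plan 28-day mortality with telephone follow-up, and no section describes how the mortality analysis set is formed. That is a fair guess at the intent, but the text does not say it, and no section cures the conflict.

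Four stronger readings are tempting, and the documents do not support them:

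- A reader might infer that all four lines can only act after randomisation. That is true of death and side effects. The 48-hour and parenteral-nutrition lines are not timed and may in part be applied at screening.
- A reader might infer that reported mortality will certainly be zero. That requires the trial to include the 28-day follow-up. The Intervention section uses the word for the treatment week, which makes the narrower loss the more natural reading.
- A reader might infer that patients who react to the tablets vanish from the safety results. This is not shown. Safety consideration has side effects reported to the ethics committee, and Table 1 has an adverse-events row.
- A reader might blame the exclusion line for survivor bias and lost power in the day-7 markers. A patient who dies before day 7 has no day-7 value whether or not the line exists, so most of that loss would remain after the line is deleted.

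An unseen analysis plan may also hold detail on imputation. That would not repair the sentence offering intention-to-treat as the remedy for missing data.

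**Conclusion.** The point holds for death and for side effects of the tablets. Both are listed as exclusions, both arise only after randomisation, and excluding such patients contradicts the stated intention-to-treat analysis. The death line also removes events from a named outcome. The 48-hour and parenteral-nutrition lines are ambiguous and need to be timed.

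This rests on the protocol's wording alone and not on any assumed figure. Its size cannot be derived from the documents. Under the assumed rates above, a true 10-point mortality difference shrinks to between 8.5 and 3.8 points as the share of excluded deaths rises from 25% to 75%, and unequal timing of deaths can create a difference of about 9 points where none exists. It should be corrected before the analysis, and preferably while patients can still be followed.

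**What to change.** 1. Remove death during the trial from the exclusion criteria.
2. Separate eligibility before randomisation from events after it. Reconcile the side-effect, 48-hour and parenteral-nutrition lines so that none of them removes a randomised patient from follow-up or analysis. When tablets are stopped is a separate clinical matter and is not judged here.
3. Analyse 28-day mortality in all randomised patients in the assigned arm, counting every death. Report side effects by arm in all randomised patients.
4. Replace the missing-data sentence. For day-7 markers and scores, analyse all available values in the assigned arm by ANCOVA adjusted for the baseline value. Add a sensitivity analysis that gives deaths before day 7 the worst rank. A likelihood-based model would add little: with one baseline and one day-7 measurement it essentially reproduces the ANCOVA in patients with day-7 values. It is the worst-rank analysis that deals with the deaths.

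The cost is protocol wording and one extra analysis, and the effect estimate may be slightly diluted. Mortality follow-up is already planned by phone. Using available day-7 values requires no new sampling, but if the team also wants day-7 blood from patients who have left the ICU, that would be extra work.

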### Randomization

Study participants who meet the inclusion criteria will be enrolled. A random number generator website will be used to randomly assign patients to intervention or control groups: https://www.sealedenvelope.com/simplerandomiser/v1/lists. Patients will be randomized into intervention or control groups with a block size of four (1:1). At randomization, individuals will be stratified by GCS (3 to 8 and 9 to 13) and age (18 to 50 and 51 to 80) so that these variables will be equally distributed between the two groups. The sequence of allocation will be determined by permuted blocks of four. A block size of four creates six different blocks for assigning patients to the trial groups. There will be identical packets and labels for intervention and placebo, each with its own sequence number. One of the investigators who is not involved in patient care will generate the allocation sequence number.

### Intervention

 Both intervention and control groups will receive standard treatments. We will use saffron and placebo (corn starch) as adjunctive therapies. A tablet containing 100 mg of saffron will be given to patients in the intervention group every day. A 100 mg tablet per day of corn starch will be administered to patients in the control group. On each day of the 7-day trial, the placebo or saffron will be administered with enteral nutrition (enteral tube feeding) once a day at 9:00. 

 Saffron and placebo tablets are prepared in packages identical to one another in terms of shape, odor, color, size, and tagged A and B. The saffron powder will be sourced from Mojtahedi Company in Mashhad. Then, experts from the Faculty of Pharmacy at medical University of Isfahan will make the supplement and placebo tablets, and perform a HPLC test. Both groups will receive nutritional support within 24–48 hr of hemodynamic stabilization. The nutritional support will be administered as a bolus method, 7 times in 24 hr, with 25 kcal/kg of energy (Fraipont and Preiser 2013). The patients will receive all commonly prescribed medicines and routine treatment, and undergo daily gastrointestinal monitoring by a physician.

### Blinding

In order to conduct a double-blind trial, A and B will be labeled on the saffron and placebo pill boxes, respectively. Until final analyses are completed, investigators, patients, their legal guardians, laboratory staff, outcome assessors, and data analysts will remain blinded to treatment assignment.

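### The Blinding section prints the pack code (A for saffron, B for placebo), which contradicts both the blinding it claims and the identically labelled, numbered packets described under Randomization

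*Protocol article*

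**What the plan says.** Three sections of the protocol article describe how the packs are identified.

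- **Randomization:** "There will be identical packets and labels for intervention and placebo, each with its own sequence number". The same section states "The sequence of allocation will be determined by permuted blocks of four", at a 1:1 ratio, within strata formed by two GCS bands and two age bands. On who makes the list: "One of the investigators who is not involved in patient care will generate the allocation sequence number".
- **Intervention:** the saffron and placebo packages are "identical to one another in terms of shape, odor, color, size, and tagged A and B".
- **Blinding:** "A and B will be labeled on the saffron and placebo pill boxes, respectively". The sentence after it says that investigators, patients, guardians, laboratory staff, outcome assessors and data analysts all stay blinded until the final analyses are done.

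No section says who may or may not see the letter on the box.

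**The concern.** There are two separate problems.

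The first is that the code is published. A letter on the box blinds only those who do not know what it stands for, and the article says what it stands for. Matching tablets for appearance and smell does not help if the outer label identifies the content. A secret key would still leave one letter shared by a whole arm, so a single lapse would reveal every patient.

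The second is that the sections cannot all be followed. Labels that are the same in both arms and differ only by a sequence number cannot also carry an arm-specific letter. Whoever prepares the packs has to choose one scheme.

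What is at stake is judgement. The Exclusion criteria ask staff to decide who is expected to die within two days and who may later be unable to take enteral feeding. They also remove patients after entry for side effects or for a switch to parenteral nutrition. Routine treatment is left open, GCS is taken from hospital records, and the Statistical methods leave the choice of test and of adjustment variables to the data. Each of these can be influenced by someone who knows or foresees the arm.

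**Working it through.** **1. The labelling statements side by side.**

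| Section | Same label in both arms? | What tells packs apart |
|---|---|---|
| Randomization | Yes | Own sequence number |
| Intervention | No | Tag A or B |
| Blinding | No | A for saffron, B for placebo |

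The first row is incompatible with the other two. The third row is also incompatible with the blinding claim that follows it, for anyone who has both the article and sight of a box.

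**2. Reach of one unmasking.** The sample size section gives 90 patients, 45 per arm. With one letter per arm, learning the treatment of one patient identifies the 45 with that letter and, by elimination, the other 45: 45 + 45 = 90. With a unique number per patient, it identifies one.

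**3. The plan's own block count.** The article says "A block size of four creates six different blocks for assigning patients to the trial groups". Check: C(4,2) = 4!/(2! × 2!) = 6. The figure is reproduced.

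**4. Predictability if the letters are visible.** Inputs: block size four, 1:1, six equally likely orders of AABB. Assumptions: the person enrolling has seen every earlier letter in that stratum, knows the block size, and guesses the letter with more places left (a tie counts as 1/2).

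| Place in block | Chance the letter is certain | Chance the best guess is right |
|---|---|---|
| 1 | 0 | 1/2 |
| 2 | 0 | 2/3 |
| 3 | 1/3 (first two letters the same) | 1/3 × 1 + 2/3 × 1/2 = 2/3 |
| 4 | 1 | 1 |

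- Certain: (0 + 0 + 1/3 + 1)/4 = (4/3)/4 = 33.3%. For 90 patients, 90 × 1/3 = 30.
- Best guess: (1/2 + 2/3 + 2/3 + 1)/4 = 2.833/4 = 70.8%, against 50% by chance.

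The count of 30 assumes complete blocks. Since 90 = 22 × 4 + 2, at least one block stays incomplete. If only one does, the expected count is 22 × 4/3 = 29.3, and it is somewhat lower if more strata end in mid-block.

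With the printed key, what is predicted is the treatment. Without the key, it is only the next letter.

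**5. The same blocks with unique numbers only.** Earlier assignments cannot be read from the packs, so nothing is left to tally: 0% certain and 50% guessed, still with blocks of four. The letters therefore cause the loss of concealment; the block size only determines how large it is.

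**The case against.** The strongest defence is that the letters may never reach the bedside. A and B could be a bulk or pharmacy code on stock boxes, from which identical numbered packets are filled for each patient. That would reconcile the three sections, and a condensed article may leave pack handling to the full protocol. The sequence also comes from an investigator outside patient care. This part stands: a reader might infer that blinding has been defeated, and the article does not show that. But nothing in the text supports the bulk-code reading either. The Blinding section offers the lettered boxes as the means of blinding, and the separation of the person who makes the list does not hide a letter on a box.

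A reader might also infer that every patient is unmasked to anyone who reads the article. That is not supported, because unmasking needs both the key and sight of the patient's box.

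A third tempting reading is that fixed blocks of four are a defect in themselves. They are not: once the letters are gone they do no harm here.

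Finally, the outcomes differ in exposure. The primary outcomes are laboratory assays run with commercial kits, specimens carry patient ID numbers, APACHE II, SOFA and NUTRIC are computed by a web-based system, and the 28-day outcome is death. These points stand and limit assessor bias. They do not protect decisions on who is enrolled, who is excluded after entry, what else is given, or how the data are analysed.

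**Conclusion.** The point holds as a contradiction in the stated blinding method. The article publishes a treatment key next to a claim of blinding, and its arm-specific tags cannot coexist with its identical numbered labels. That much needs no assumption.

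The size of the consequence is conditional. One lapse exposes all 90 patients under a two-letter code. The 33% and 71% figures are an upper-end case: they need recruiters who see every earlier letter in each of the four strata and know the block size, and they assume complete blocks. The exposure is mainly in enrolment and exclusion judgements, co-treatment, GCS and analysis choices, and is smaller for the assays. It should be settled before patients are enrolled, since a broken blind cannot be restored afterwards.

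**What to change.** Reconcile the Randomization, Intervention and Blinding sections on one scheme:

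- Remove the A and B tags and the printed key.
- Label each pack only with its unique sequence number, as Randomization already describes.
- Keep the list linking numbers to treatment with the uninvolved person who generates it.
- Give the analysts a dummy arm code that has no relation to any pack label.

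Randomly varying, undisclosed block sizes are an optional further safeguard. They may allow slightly more imbalance within a stratum and would need a new list from the same website.

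The required change costs the relabelling of the packs and a few corrected sentences. It affects neither the sample size nor the analysis.
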